#### 2.1.2 Secondary objective

The secondary objective of this study was to identify differential metabolites in the serum and urine of patients before and after JTTF treatment to determine possible relevant metabolic pathways and routes of action in T2DM combined with NAFLD. Furthermore, we explored the regulatory effects and mechanisms of JTTF action on various aspects including lipid and glucose regulation at the metabolic level.

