### 2.2 Study design

This study is designed as a 12-weeks, single-center, double-armed, parallel, randomized, controlled clinical trial. A total of 96 eligible participants will be recruited from Shenzhen Hospital of Guangzhou University of Chinese Medicine (Futian) and randomized in a 1:1 ratio into two groups to receive basic treatment. As a supplement to the clinical study, participants’ fasting serum and urine samples will be subjected to untargeted and targeted metabolomic assays. Liquid chromatography–mass spectrometry (LC-MS) will be used to compare metabolites before and after treatment in the experimental and control groups. Basic analysis of metabolites, multivariate statistical analysis, pathway enrichment analysis, and topological analysis of the screened differential metabolites will be performed.

All patients should have voluntarily participated and signed an informed consent form with good compliance. Informed consent will be obtained from all participants prior to enrollment. A flowchart and schedule of the clinical trial is shown in Figure 1 and Table 1, respectively. The protocol was designed according to the Standard Protocol Items: Recommendations for Interventional Trials (SPIRIT) guidelines (Chan et al., 2013) and the Declaration of Helsinki. The SPIRIT checklist is shown in Supplementary Material S2.

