#### 2.8.5 Biological specimen analysis outcomes

Untargeted and targeted metabolomics tests will be performed sequentially on fasting blood and urine samples collected at enrollment and at the end of the 3-month treatment period. Biological samples will be centrifuged and stored in a -80°C refrigerator. Assays will be performed using liquid chromatography-mass spectrometry (LC-MS) techniques for microscopic high-throughput measurements. Through basic analysis, multivariate statistical analysis, and difference analysis, the differential metabolites in serum and urine, before and after treatment, will be compared between the two groups. Further targeted metabolomic analyses will be performed to categorize differential metabolites screened by untargeted metabolomics, as well as explore their possible metabolic pathways. The exploratory results will be combined with clinical efficacy evaluation to determine the mechanism of action of JTTF in the treatment of T2DM complicated with NAFLD from the perspective of metabolomics and small-molecule compounds.

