## 3 Statistical methods

### 3.1 Data analysis

Data will be analyzed using SPSS software (Version 24.0; IBM Corp. Armonk, NY, United States). Continuous variables will be represented as means, standard deviations, medians, and minimum/maximum values. If the data confirms normal distribution, an independent sample *t*-test will be used to assess the differences between the two groups, and a paired sample *t*-test to compare the differences between groups before and after the intervention. Wilcoxon signed-rank test will be used for data that does not conform to normal distribution. Grade data will be analyzed using Wilcoxon’s signed-rank test or the CMHχ2 test. Statistical significance will be set at *p* < 0.05.

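### The metabolomics objective is worded as an uncontrolled before/after contrast that conflicts with the outcome section, and the only significance rule available to the untargeted screen is an unadjusted p < 0.05

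*Protocol article*

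**What the plan says.** The protocol article describes the metabolomics contrast in three places, and the wording differs.

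- Section 2.1.2 (secondary objective): the aim is to "identify differential metabolites in the serum and urine of patients before and after JTTF treatment". The control arm is not mentioned.
- Section 2.2 (study design): LC-MS will be used to "compare metabolites before and after treatment in the experimental and control groups". Both arms appear, but the text does not say whether the arms are compared with each other.
- Section 2.8.5 (biological specimen analysis): "the differential metabolites in serum and urine, before and after treatment, will be compared between the two groups". This is a between-group comparison.

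On method, section 2.2 says: "Basic analysis of metabolites, multivariate statistical analysis, pathway enrichment analysis, and topological analysis of the screened differential metabolites will be performed". Section 2.8.5 adds a second stage: "Further targeted metabolomic analyses will be performed to categorize differential metabolites screened by untargeted metabolomics". Neither section gives a threshold for calling a metabolite differential. The only specimens described are the trial's own enrolment and three-month samples. On use, section 2.8.5 says: "The exploratory results will be combined with clinical efficacy evaluation to determine the mechanism of action of JTTF".

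Section 3.1 is the only section on data analysis. It fixes one rule, "Statistical significance will be set at" p < 0.05, and states no exception. It also names a paired t-"test to compare the differences between groups before and after the intervention", a phrase that mixes a within-arm and a between-arm comparison.

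**The concern.** Two features of the text could each put wrong entries on the metabolite list.

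**Contrast.** Section 2.7 gives both arms conventional basic treatment and the same education, diet and exercise support. A metabolite that moves over 12 weeks for any of these reasons will also move in the JTTF arm. Under the wording of section 2.1.2 it counts as differential, although randomisation would show no difference between arms. A multiplicity correction does not help, because the change is real but is not due to JTTF.

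**Threshold.** An untargeted LC-MS screen tests many features in two fluids. A 5% rule per test suits a single clinical endpoint. Used on every feature, it selects 5% of those that did not change.

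Identifying differential metabolites is the first stated aim of the secondary objective, and the list feeds pathway enrichment, the targeted assay and the mechanistic interpretation. Re-measuring the same samples removes neither error: a chance imbalance between arms, or a change from background care, is still present in those samples.

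**Working it through.** The plan gives no figure for the metabolomics analysis, so there is none to reproduce.

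**Inputs**
- Evaluable size (section 2.10): 76 in total, so 76/2 = 38 per arm. The allowance for dropout agrees: 38/(1 − 0.20) = 47.5, rounded up to 48 per arm, 96 in total.
- Threshold (section 3.1): p < 0.05, taken as two-sided.
- Assumed, because not stated: m = 1,000 to 5,000 features per fluid; a shared change of 0.2, 0.3 or 0.5 SD of the change; for step 4, the share of features truly different and the effect size.

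**Step 1. Before/after test in the JTTF arm when JTTF has no effect.** A paired t-test with n = 38 has 37 degrees of freedom and noncentrality d × √38 = 6.164 d, where d is the shared change in SDs of the change.

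| Shared change d | Noncentrality | Probability of p < 0.05 in the JTTF arm |
|---|---|---|
| 0 | 0 | 0.05 |
| 0.2 | 1.23 | 0.22 |
| 0.3 | 1.85 | 0.44 |
| 0.5 | 3.08 | 0.85 |

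A between-arm test of the change would select such a metabolite 5% of the time, because the arms do not differ.

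**Step 2. Comparing two within-arm lists.** If a metabolite were called a JTTF effect because it is significant in that arm and not in the control arm, the probability with equal true change and 38 in each arm is P(1 − P): 0.22 × 0.78 = 0.17, 0.44 × 0.56 = 0.25 and 0.85 × 0.15 = 0.13 for d = 0.2, 0.3 and 0.5. All exceed 0.05, so comparing lists does not repair the contrast.

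**Step 3. Chance hits under a flat 5% rule.** Expected false selections per fluid if no feature differs = 0.05 × m. For m = 1,000 this is 50; for m = 5,000 it is 250. Over serum and urine the totals are 100 to 500. Correlation among features leaves this expectation unchanged, though it makes the actual count more variable.

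**Step 4. Illustrative false share of a between-arm list.** With a share π truly different and power w, the false share is 0.05(1 − π)/[0.05(1 − π) + wπ]. For a true difference of 0.6 SD and 38 per arm, w = 0.733:
- π = 0.05: 0.0475/(0.0475 + 0.0367) = 0.56
- π = 0.10: 0.0450/(0.0450 + 0.0733) = 0.38
- π = 0.20: 0.0400/(0.0400 + 0.1466) = 0.21

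With w = 0.80 the values are 0.54, 0.36 and 0.20. Selection at a 5% false discovery rate aims to hold this share at about 0.05.

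**The case against.** The case against has four parts.

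1. **The threshold.** Section 3.1 does not mention metabolomics. Its tests are those of clinical endpoints, and sections 2.2 and 2.8.5 give metabolomics its own analysis route, including multivariate analysis. A reader might infer that the plan expressly screens every LC-MS feature at p < 0.05; it does not say so. A selection rule may also sit in a full protocol or analysis plan that is not shown. This stands as a limit on the claim: p < 0.05 applies by default, as the only rule written.

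2. **The contrast.** A reader might infer from section 2.1.2 that the trial is committed to a before/after analysis of the JTTF arm alone, or that it will compare two within-arm lists. Section 2.8.5 most naturally reads as a comparison of changes between groups, section 2.2 includes the control arm, and no sentence says that a metabolite is selected because it is significant in one arm only. What remains is a conflict between the objective and the outcome section, which an analysis plan built on the objective would inherit.

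3. **Background care.** It is tempting to say that both arms newly start drugs and lifestyle measures at baseline. The text does not support this. Section 2.7 says only that both arms receive them, and the abstract places the same lifestyle interventions in the preceding 12 weeks. A shared change is therefore possible, but its size is unknown.

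4. **The stakes.** Section 2.8.5 calls the results exploratory and combines them with the clinical evaluation, and metabolomics is not a primary outcome. That limits the consequences. It does not settle the matter, because the same sentence uses the results to determine the mechanism of action.

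**Conclusion.** The point holds in a limited form and should be corrected. Section 2.1.2 states an uncontrolled within-arm contrast that conflicts with section 2.8.5. If it were followed, a change of 0.3 to 0.5 SD shared by both arms would be credited to JTTF with probability about 0.44 to 0.85, given 38 patients in the arm. Those change sizes are assumptions.

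The unadjusted p < 0.05 in section 3.1 is the only significance rule in the document and so the default for the untargeted screen. Applied feature by feature, it gives 50 to 250 chance hits per fluid for an assumed 1,000 to 5,000 features with no true difference.

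The false shares of 38% to 56% in step 4 should not be read as a prediction for this trial. They depend on an assumed true share of 5% to 10% and an assumed effect of 0.6 SD, they describe univariate between-arm screening and not within-arm selection, and they fall to 21% if 20% of features truly differ. The primary outcomes are not affected.

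**What to change.** 1. In section 2.1.2, define a differential metabolite as one with a between-arm difference in the week-12 level adjusted for baseline, or equivalently framed as an arm-by-time interaction. Word section 2.8.5 so that it can only mean this contrast. Changes within the JTTF arm can still be reported descriptively.
2. In section 3.1, state that the untargeted screen is an exception to p < 0.05, with selection within each fluid by Benjamini-Hochberg at a 5% false discovery rate. If a fuller plan already contains such a rule, one sentence pointing to it is enough.
3. In section 2.8.5, describe the targeted assay on the same samples as quantification of the selected metabolites, not as independent confirmation.

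The cost is a few sentences and one standard adjustment in the software, with no new samples, visits or patients. The downside is a shorter metabolite list: with about 38 per arm, some metabolites with modest true differences will no longer be selected. Both main changes are needed, because false discovery control does not correct a within-arm contrast, and a between-arm contrast does not limit chance hits.

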### 3.2 Monitoring

To maintain high-quality data and ensure the smooth running of the trial, all protocol implementers and investigators will undergo systematic and rigorous training. Patient screening, data entry, dosing, adverse event reporting, dosing records, and biospecimen extraction will be performed. The data of numbered participants will be recorded in detail on standardized CRF forms and biospecimens will be stored under the same number. Data will be recorded independently by two research assistants, updated in real time, and synchronized on the CRF form after each visit. Quality control and data review will be performed regularly by the study monitoring committee to ensure accuracy and completeness of data entry. The quality and progress of the project will be evaluated. An interim analysis of the primary outcome will be conducted to monitor efficacy and safety when 50% enrollment is reached. This is independent of the sponsor. All patient information and clinical data will be kept confidential on a professional data platform.

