**FIGURE 1 F1:**
[figure not shown]
Flow chart of the clinical trial.

**TABLE 1 T1:** Schedule of the clinical trial.

Project time	Screening/baseline		Treatment			
	-14–0 days	0±2 days	Visit 1 4weeks± 2days	Visit 2 6weeks± 4days	Visit 3 8weeks± 6days	Visit 4 12weeks± 7days
Eligibility screening						
Inclusion/exclusion criteria	**✓**					
Informed consent form	**✓**					
Allocation	**✓**					
General information	**✓**					
Family history	**✓**					
Medical history	**✓**					
Drinking history	**✓**					
Physical examination^a^	**✓**	**✓**	**✓**	**✓**	**✓**	**✓**
Vital signs^b^	**✓**	**✓**	**✓**	**✓**	**✓**	**✓**
Ultrasound of liver	**✓**					**✓**
bioelectrical impedance analysis						
visceral fat area		**✓**				**✓**
subcutaneous fat area		**✓**				**✓**
Electrocardiography	**✓**			**✓**		**✓**
Laboratory examination						
Routine blood test		**✓**		**✓**		**✓**
Routine urine test		**✓**		**✓**		**✓**
Fasting blood sugar		**✓**		**✓**		**✓**
2-h plasma glucose		**✓**				**✓**
Glycated hemoglobin		**✓**				**✓**
Fasting insulin		**✓**				**✓**
Blood lipids		**✓**		**✓**		**✓**
Liver function		**✓**		**✓**		**✓**
Renal function		**✓**		**✓**		**✓**
Traditional Chinese medicine symptoms		**✓**	**✓**	**✓**	**✓**	**✓**
Fibrosis 4 Score		**✓**				**✓**
Homeostasis model assessment-insulin resistance		**✓**				**✓**
homeostatic model assessment for β-cell		**✓**				**✓**
Metabolomics test^c^						
Serum sample		**✓**				**✓**
Urine sample		**✓**				**✓**
Adverse event			**✓**	**✓**	**✓**	**✓**
Prescription		**✓**	**✓**	**✓**	**✓**	**✓**
Combined drugs		**✓**	**✓**	**✓**	**✓**	**✓**
Summary of the analysis						**✓**

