#### 2.8.2 Primary outcomes

The primary outcome is change in visceral fat area (VFA) and TCM syndromes efficacy score scale. Changes in VFA will be compared between the two groups before and after treatment. The indicator will be tested at baseline and week 12. The TCM symptom scoring standard is presented in Supplementary Material S3.

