### 2.10 Sample size calculation

In a previous study (Xu, 2017), JTTF reduced HbA1c levels in diabetic patients with heat stagnation in liver and stomach after 12 weeks of treatment (treatment group: 6.94±0.88%, control group: 7.64±0.72%, mean difference between the two groups: 0.7%). Considering a type I error of 5% (α = 0.05) and a power of 85%, the experimental and control groups were allocated at a ratio of 1:1. The sample size was calculated using Power Analysis and Sample Size (PASS) software (version 15.0); a total of 76 patients will be required. According to the dropout rate of 20%, we set the final sample size to 96, with 48 patients in each group, considering the number of dropout samples.

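### The efficacy look at 50% enrolment leaves the 5% type I error unprotected as written, and its enrolment trigger does not suit a visceral fat outcome measured only at week 12

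*Protocol article*

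**What the plan says.** Section 3.2 (Monitoring) commits to one interim look: "An interim analysis of the primary outcome will be conducted to monitor efficacy and safety when 50% enrollment is reached". It adds that this is independent of the sponsor. It gives no threshold for the look and does not say what the result may lead to.

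Section 3.1 (Data analysis) gives a single level: "Statistical significance will be set at *p* < 0.05". Section 2.10 (Sample size calculation) plans with "Considering a type I error of 5% (α = 0.05) and a power of 85" per cent, for a total of 96 participants after allowance for 20% dropout.

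Section 2.8.2 defines what the look would examine: "The primary outcome is change in visceral fat area (VFA) and TCM syndromes efficacy score scale". On VFA it says: "The indicator will be tested at baseline and week 12". Table 1 agrees, with VFA ticked only at baseline and at the week-12 visit. The row "Traditional Chinese medicine symptoms" in Table 1 is also ticked at weeks 4, 6 and 8.

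**The concern.** There are two linked problems.

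**Error rate.** The document names an efficacy look at the primary outcome, one significance level and a 5% type I error. These are compatible only if the interim look cannot lead to an efficacy claim, or if the two looks share the 5%. The text states neither. If p < 0.05 were applied at both looks, a false claim of efficacy would be more likely than the design figure implies.

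**Trigger.** The look is tied to the number enrolled, but the VFA outcome arrives 12 weeks after entry. Half the participants enrolled is therefore not half the VFA information. The look would rest on the earliest entrants only. This is an open-label trial (section 2.9) with a symptom score as the other primary outcome, so an early efficacy result that became known could affect later conduct and scoring.

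**Working it through.** **Inputs**
- Alpha 0.05 (section 2.10) and threshold p < 0.05 (section 3.1). Sidedness is not stated; two-sided is assumed, so the critical value is 1.96.
- Total 96: 76/(1 − 0.20) = 95, rounded up to 48 per arm = 96. This reproduces the dropout step in section 2.10. Half enrolment is 48.
- VFA at baseline and week 12 only (section 2.8.2, Table 1).
- Recruitment duration: not given. Section 5 has only an expected end date. Uniform recruitment over T = 26, 39, 52, 78 and 104 weeks is assumed, to show a range.

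**Step 1: the plan's own figure.** One final test, rejecting when |Z| > 1.96, has a type I error of 0.05. The 5% is right for a single look.

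**Step 2: two looks, each at 0.05.** Let Z1 and Z2 be the interim and final statistics and t the information fraction at the interim. Under the null hypothesis they are bivariate normal with correlation √t. If efficacy can be claimed at either look:

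type I error = 1 − P(|Z1| < 1.96 and |Z2| < 1.96)

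At t = 0.5 the correlation is 0.707 and the result is 0.083.

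**Step 3: week-12 VFA results at the 48th enrolment.** Recruitment runs at 96/T per week, so 48 are enrolled at week T/2. Those with 12 weeks of follow-up number 96 × (T/2 − 12)/T. Dividing by 96 gives t. Dropout at an equal rate would lower the counts but not t.

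| T (weeks) | Calculation | With week-12 VFA, before dropout | t | Type I error, both looks at 0.05 |
|---|---|---|---|---|
| 26 | 96 × 1/26 | about 4 | 0.04 | 9.6% |
| 39 | 96 × 7.5/39 | about 18 | 0.19 | 9.2% |
| 52 | 96 × 14/52 | about 26 | 0.27 | 9.0% |
| 78 | 96 × 27/78 | about 33 | 0.35 | 8.8% |
| 104 | 96 × 40/104 | about 37 | 0.38 | 8.7% |

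Whatever the rate, anyone enrolled in the preceding 12 weeks has no week-12 value, so the count is below 48 and t is below 0.5. The inflation grows as t falls because the two statistics become less correlated.

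**Step 4: thresholds that hold 5%.** At t = 0.5, O'Brien-Fleming-type spending gives critical values 2.963 and 1.969. These correspond to two-sided p of about 0.003 and 0.049, and the formula in Step 2 then returns 0.050. The classical O'Brien-Fleming constants (p < 0.0052, then p < 0.0480) also hold 5%. The choice between them is one of convention.

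**The case against.** The strongest reply is that this is a condensed article. Interim boundaries and alpha spending usually sit in the full protocol, the analysis plan or a monitoring charter, none of which is shown. Their absence here is not a fault, and that stands. A reader might infer that the trial will test efficacy at the interim with no adjustment, and that the 5% therefore fails. The document does not say so. Section 3.1 does not mention the interim, section 2.10 gives alpha only as an input to the sample size, and section 3.2 speaks of monitoring efficacy, not of claiming it. If the look can lead only to action on safety or futility, the final test at 0.05 is not inflated.

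A reader might also infer that very few week-12 results will exist at the look. That depends on a recruitment rate that is not given: about 4 if recruitment takes 26 weeks, but about 26 of the 48 enrolled if it takes 52. Only the statement that fewer than 48 will have the result is certain. It is firmest for VFA, since the symptom score has earlier visits, although its week-12 change is also missing for recent entrants. The sponsor could wait for the first 48 to finish follow-up, but section 3.2 sets the time by enrolment.

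It is tempting to add the inflation from two primary outcomes. The document does not say that either one suffices, and that is a separate matter, not counted here.

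Section 3.2 also makes the look independent of the sponsor, and section 2.9 blinds analysts and statisticians. These reduce the risk to trial conduct. They do not set an interim level or say who sees the result.

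**Conclusion.** The concern holds in conditional form. The text commits to an efficacy look and gives one significance level, so the 5% is not protected as written. The 8.3% at half information, and the 8.7% to 9.6% at the lower fractions, rest on three assumptions: two-sided tests, p < 0.05 applied at both looks, and efficacy claimable at either. The document neither states nor excludes the last two.

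The trigger problem does not depend on those assumptions. Enrolment of 48 gives less than 50% of the VFA information at any recruitment rate; how much less depends on the assumed duration. An unseen analysis plan could supply boundaries, but changing the trigger would mean overriding section 3.2.

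This should be fixed before the look takes place. Confidence is moderate.

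**What to change.** Choose one of two changes and state it in sections 3.2 and 3.1.

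1. **Safety and conduct only.** State that the look at 50% enrolment covers safety and trial conduct, with no between-arm efficacy test of VFA or the symptom score. The final test stays at p < 0.05. The cost is giving up an early efficacy claim.
2. **A proper efficacy look.** Trigger it when 48 participants have a week-12 VFA. Use O'Brien-Fleming-type spending, about p < 0.003 at the interim and p < 0.049 at the end, with the boundary recalculated from the actual information fraction. State what the result may lead to and who sees it. The cost is a later look and a final threshold of 0.049 instead of 0.05.

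Either change takes a sentence or two. If a boundary already exists in the full protocol or analysis plan, cite it in section 3.2 and correct the trigger.
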